---

## 1. **SYNOPSIS**

1. Sponsor identification: SAEI  
Sociedad Andaluza de Enfermedades Infecciosas  
(Andalusian Society of Infectious Diseases)
2. Title of clinical trial: A randomized, open label clinical trial to compare the quality of life of HIV+ patients who start monotherapy with LPV/r tablets versus triple therapy containing a boosted PI.
3. Protocol code: SAI-CDV-2009-01
4. EudraCT code: 2009-014430-25
5. Name and qualification of monitors: Effice spi S.L.  
[name]  
[name]
6. Phase of clinical trial: Phase IV
7. Objectives  
Primary objective: To compare the quality of life of patients who start monotherapy with lopinavir/ritonavir® (LPV/r) tablets versus patients on triple therapy containing any boosted protease inhibitor (PI).  
Secondary objectives:
  1. Assessment of virological efficacy of monotherapy based on LPV/r tablets versus triple therapy containing any PI.
  2. Assessment of changes in immune response in HIV+ patients who start monotherapy with LPV/r tablets versus triple therapy containing any PI.
  3. Assessment of treatment satisfaction of HIV+ patients who start monotherapy with LPV/r tablets versus triple therapy containing any PI.
  4. Assessment of treatment adherence of HIV+ patients who start monotherapy with LPV/r tablets versus triple therapy

containing any PI.

5. Assessment of regimen tolerability and safety in HIV+ patients who start monotherapy with LPV/r tablets versus triple therapy containing any PI.

8. Design: A Phase IV national, multicenter, controlled, randomized, open label, parallel-group, comparative clinical trial

9. Randomization process: Randomization will be centrally performed.

10. Treatment groups: Treatment:  
Patients will be randomized in a 1:2 ratio to two groups, A and B respectively.

**Control group (A):** Patients will continue on triple antiretroviral therapy based on any PI boosted with ritonavir.

**Experimental group (B):** Triple antiretroviral therapy based on any PI boosted with ritonavir will be switched to LPV/r monotherapy.

Central randomization will be performed.

11. Disease under study: HIV infection

12. Primary endpoint: Quality of life, as measured by the MOS-HIV and EQ-5D questionnaires, of patients who start monotherapy with lopinavir/ritonavir (LPV/r) tablets versus patients on triple therapy containing any boosted protease inhibitor (PI).

13. Number of subjects: 390 (260 in experimental group B and 130 in control group A)

14. Selection criteria:

Inclusion criteria:

- Patients infected with HIV-1, as documented by a positive HIV-1 antibody test and/or a documented positive PCR for HIV-1 RNA.
- Patients on antiretroviral triple therapy containing any boosted PI.
- Patients with an undetectable viral load, defined as < 50 copies/mL of HIV RNA in the past 6 months.
- Males or females aged  $\geq 18$  years.
- For women of childbearing age, a negative urine pregnancy test at the screening visit.
- Patients who have given written informed consent before undergoing any study-specific screening procedure.

Exclusion criteria:

- Patients with documented record, in the resistance accumulated genotyping, of mutations that confers loss of susceptibility to LPV/r. Or, in the absence of genotyping, evidence of having failed to therapy with protease inhibitors (PI)
- Patients with a CD4 cell nadir <100 cel/ $\mu$ L.
- Patients who cannot be treated with LPV/r® for any reason.
- History of psychiatric disorders such as depressive syndrome, schizophrenia, or psychotic disease.
- Known history of drug addiction or chronic alcohol consumption that contraindicates participation in the study in the investigator's criterion.
- Pregnant or nursing women or women of childbearing age not using an adequate contraceptive method according in the investigator's criterion.
- Current active opportunistic infection or documented

infection within 4 weeks of screening.

- Patients in whom modification or withdrawal of any component of the current antiretroviral triple therapy is planned due to serious toxicities related to any component of such therapy.
- Patients in whom investigators consider that antiretroviral medication should be changed for any reason in the next 6 months.
- Renal disease with creatinine clearance < 60 mL/min.
- Concomitant use of drugs contraindicated with LPV/r® such as rifampin, dihydroergotamine, ergotamine, methylergonovine, cisapride, St. John's wort, lovastatin, simvastatin, pimozide, midazolam, and triazolam.
- Concomitant use of nephrotoxic or immunosuppressive agents.
- Patient on current treatment with systemic corticosteroids, interleukine-2, or chemotherapy.
- Patients treated with other investigational agents.
- Patients with acute hepatitis.
- Any disease that, in the investigator's judgment, contraindicates patient participation in the study.

15. Treatment duration: 24 weeks.

16. Timetable and expected completion date: The approximate recruitment time will be 6 weeks.  
Treatment duration will be 24 weeks.  
Start of recruitment: November 2009.  
End of recruitment: June 2010.  
End of follow-up of last patient: December 2010.  
Final report: March 2011.

## 2. **LIST OF ABBREVIATIONS**

|         |                                                           |
|---------|-----------------------------------------------------------|
| 3TC     | Emtricitabine                                             |
| AE      | Adverse events                                            |
| ART     | Antiretroviral therapy                                    |
| AZT     | Zidovudine                                                |
| AZT/3TC | Combivir                                                  |
| CREC    | Clinical Research Ethics Committee                        |
| CRF     | Case Report Form                                          |
| CRO     | Contract Research Organization                            |
| EQ-5D   | EuroQol 5-D                                               |
| HAART   | Highly active antiretroviral therapy                      |
| HIV-1   | Acquired immunodeficiency virus                           |
| LPV/r   | Lopinavir/ritonavir.                                      |
| MOS_HIV | Medical Outcome Study in HIV                              |
| NNRTIs  | Non-nucleoside analogue reverse transcriptase inhibitors  |
| NRTIs   | Nucleoside analogue reverse transcriptase inhibitors      |
| PCR     | Polymerase chain reaction                                 |
| PI      | Protease Inhibitors                                       |
| QoL     | Quality of life                                           |
| RTV     | Ritonavir                                                 |
| SAE     | Serious adverse events                                    |
| SAMPMD  | Spanish Agency for Medicinal Products and Medical Devices |
| TDF     | Tenofovir                                                 |
| TDF+3TC | Truvada                                                   |
| VAS     | Visual analog scale                                       |

### **3. GENERAL INFORMATION**

#### **A. Trial identification**

- 1.- Protocol code: SAI-CDV-2009-01
- 2.- EudraCT code: 2009-014430-25
- 3.- Title: A randomized, open label clinical trial to compare the quality of life of HIV+ patients who start monotherapy with LPV/r tablets versus triple therapy containing a boosted PI.

- B. Type of clinical trial: A Phase IV multicenter, national, randomized, open label, prospective study.

- C. Description of test products: Kaletra®: (Lopinavir/ritonavir).  
Film-coated tablets containing 200 mg of lopinavir co-formulated with 50 mg of ritonavir.  
Administration route: Oral.  
Therapeutic group: Protease Inhibitor (J05AE06)

- D. Sponsor data: SAEI  
Soc.Andaluza de Enfermedades Infecciosas  
(Andalusian Society of Infectious Diseases)  
[name]  
Teléfono: [name]  
e-mail:[contact]
- E. Monitor identification: Effice spi S.L.  
[name]  
[name]

## **4. RATIONALE AND OBJECTIVES**

### **4.1 RATIONALE**

Current antiretroviral treatment for HIV-infected adults is based on the combination of two nucleoside analogue reverse transcriptase inhibitors (NRTIs) combined with a non-nucleoside analogue reverse transcriptase inhibitor (NNRTI) or a protease inhibitor (PI) boosted with a low dose of ritonavir (RTV) [1].

Despite the great success of highly active antiretroviral therapy (HAART), triple therapy regimens are associated to long-term toxicity, high costs, and a complex administration that may have direct consequences for HIV-infected patients because of a decreased treatment adherence, treatment dissatisfaction, the negative impact caused on quality of life (QoL), and above all because it could affect treatment efficacy [1-5].

Triple therapy based on NRTIs and a PI has been associated to a number of significant metabolic adverse effects such as body fat redistribution (lipoatrophy of the face and limbs, central obesity) and hyperlipidemia (hypercholesterolemia and hypertriglyceridemia). Although the great majority of metabolic adverse effects were initially attributed to use of PIs, the hypothesis that adverse effects such as lipoatrophy are more related to antiretroviral therapies containing NRTIs than to PIs has gained weight over the years. In the Prometheus study [6], a greater incidence of lipoatrophy was seen in patients treated with nucleosides as compared to those receiving two PIs (ritonavir and saquinavir combined).

Another significant adverse effect of HAART is a form of lactic acidosis causing a high mortality [7]. It is currently accepted that severe lactic acidosis in patients receiving two nucleosides and a PI is due to the mitochondrial toxicity induced by nucleosides, particularly d4T.

Use of a PI boosted with RTV may also complicate the treatment regimen for some patients. This PI-based regimen not only requires additional administration of RTV capsules, but also special storage conditions due to the recommendation of maintaining the capsules refrigerated [8]. Kaletra® is a LPV/r co-formulation with a high antiviral potency which has been shown to have long-term efficacy and safety in combination with other antiretroviral agents [9].

LPV/r is characterized by a very high pharmacological and genetic barrier. Trough plasma levels of LPV/r are more than 70-fold higher than the EC50 for wild-type HIV. Occurrence of resistance to LPV/r requires accumulation of mutations in the protease gene. The EC50 for wild-type HIV starts to show a clinically significant increase from five mutations [10-11]. In

study 863, none of the patients treated with LPV/r with a viremia rebound to more than 400 copies/mL developed mutations in the protease gene [12].

In addition, the new formulation of LPV/r as tablets decreases pill overload and also eliminates the requirement of refrigeration. Administration of medication with food is not required either [9].

Together, these advantages promote simplification of antiretroviral therapy and a potential improvement in adherence. In recent years, data have been reported on use of LPV/r monotherapy as starting treatment [13], as maintenance after initial therapy [14], and as maintenance following HAART with undetectability sustained for at least 6 months [15-17].

The third approach is the one that has been shown to date to be safest for use of LPV/r as monotherapy, based on reported data from the OK04 study (a randomized, comparative study on 200 patients) at 48 weeks [15] and at 96 weeks [18].

In another open label study (MONARK) in which naïve patients were randomized to receive monotherapy based on LPV/r® or standard antiretroviral triple therapy using LPV/r (Kaletra®)+ AZT/3TC (Combivir®), virological efficacy was similar in both groups at 48 weeks of treatment even in patients in the monotherapy group who had episodes of lower viremia levels [5]. In addition, the mean total symptoms reported and the number of symptoms causing discomfort were significantly higher in the triple therapy group as compared to the monotherapy group (relative risk 1.3 and 1.4; P= 0.001 and P= 0.0003 respectively), and the proportion of patients with a positive perception of their overall quality of life increased in the monotherapy group from 32% at baseline to 68% at 48 weeks of study (P<0.0001), and in the triple therapy group from 46% to 59% (P= 0.38) [5].

Finally, in a randomized, open label, 48-week study in HIV+ patients with an inhibited viral replication switched from antiretroviral triple therapy based on LPV/r to monotherapy based on LPV/r, the proportion of patients who maintained an undetectable viral load in the monotherapy group was not statistically different from that of patients from the group continuing on triple therapy (81% vs 95%, P=0.34) [5].

### **Rationale for the study:**

Over the past years, the simplification approach of LPV/r as monotherapy has been shown to be not inferior to triple therapy in virological and immunological efficacy.

In Spain, use of simplification to LPV/r monotherapy has been included since January 2008 in treatment guidelines as a therapeutic option for patients with no history of prior PI failure, an undetectable viral load for at least 6 months, and signs and/or symptoms of toxicity from NRTIs [19].

The purpose of this randomized, open label, 24-week study is to compare the quality of life of patients who start monotherapy with co-formulated LPV/r tablets as compared to patients with HAART based on any boosted PI.

## **4.2 STUDY OBJECTIVES:**

### Secondary objectives:

#### **4.2.1. Primary objective:**

- To compare the quality of life of patients who start simplification to monotherapy with lopinavir/ritonavir (LPV/r) tablets versus patients who continue on triple therapy containing any boosted protease inhibitor (PI).

#### **4.2.2. Secondary objectives:**

- Assessment of treatment satisfaction of HIV+ patients who start simplification to monotherapy with LPV/r tablets versus triple therapy containing any PI.
- Assessment of treatment adherence of HIV+ patients who start simplification to monotherapy with LPV/r tablets versus triple therapy containing any PI.
- Assessment of regimen tolerability and safety in HIV+ patients who start simplification to monotherapy with LPV/r tablets versus triple therapy containing any PI.
- Assessment of virological efficacy of simplification to monotherapy based on LPV/r tablets versus triple therapy containing any PI.
- Assessment of changes in immune response in HIV+ patients who start simplification to monotherapy with LPV/r tablets versus triple therapy containing any PI.

## **5. CLINICAL TRIAL TYPE AND DESIGN**

### **5.1 DESIGN**

A Phase IV multicenter, national, randomized, open label, prospective study in HIV+ patients on antiretroviral triple therapy containing any boosted protease inhibitor (PI), as compared to patients who start simplification to monotherapy with LPV/r tablets.

### **5.2 PATIENT ENROLLMENT**

When a patient is considered to be eligible for the study, he/she will be asked to participate in it, for which the patient information sheet (Appendix 3) and any additional information that may be required will be provided. Once informed consent is obtained from the patient, the patient enrollment form, will be faxed to the Study Data Center in order to obtain patient randomization and a patient screening number:

[For more information, please see section 5.3 “patient randomization”.

The following data will be recorded in the enrollment form:

- Rank number of selection at the patient center.
- Investigating center
- Investigator

### **5.3 PATIENT RANDOMIZATION**

Randomization will be centralized and will be performed from the study data center upon data reception. Central randomization will be performed.

Before patients begin the study, patients will be randomized according to a randomization list. The list will be created by generating pseudo-random numbers of Wichmann and Hill (1982) and modified by McLeod (1985). The size of the blocks will be 4 to try to balance the treatment arms of the total sample and within each center. No stratification was planned by any other factor

The randomization list will be centralized and hidden from the investigators. Investigators will access the allocated treatment by telephone at the time of randomization with the sponsor or who is assigned on its behalf. CRD corresponding page will be sent by fax prior to the phone call. CRD corresponding page confirms that the patient meets all inclusion criteria and none of exclusion in order to know the branch of study is given and the number of patients used for

the same. This information is written back to the researcher in the same format for receiving your application, including the number assigned to the patient and the branch of study.

Patients will be randomized in a 1:2 ratio to one of the following two options:

**Control group (A):** Patients will continue on antiretroviral triple therapy based on any PI boosted with ritonavir.

**Experimental group (B):** Patients will be switched from antiretroviral triple therapy based on any PI boosted with ritonavir to LPV/r monotherapy (co-formulated tablets).

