## **6. SUBJECT SELECTION**

### **6.1 PLANNED NUMBER OF SUBJECTS**

A total of **390 patients** will be enrolled into this study (130 patients in control group A and 260 patients in experimental group B).

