### ***Sample size and rationale***

In a similar study population (e.g. HIV+ patients with an undetectable viral load, i.e. < 50 copies/mL of HIV-1 RNA), the mean baseline quality of life score measured with the MOS-HIV questionnaire was 61.84 [24]. As standard deviation is not available, we assume for all calculations that standard deviation will be the highest score minus the lowest score in the quality of life dimension (e.g. 100) divided by 5, which gives 20. This standard deviation of 20 is the same as found in HIV-infected asymptomatic patients, patients with AIDS-related symptoms, or patients with AIDS and a CD4 cell count <100 [25]. Assuming, then, that quality of life will remain unchanged in patients assigned to the control group (maintaining current antiretroviral therapy) and will improve by 10% (e.g. to scores of 68.02) in patients assigned to the experimental group (LPV/r® as monotherapy), with a 1:2 ratio, an 80% statistical power, and a two-sided alpha of 0.05, 372 patients would be required, 248 randomized to the experimental group and 124 randomized to continue on the current antiretroviral therapy.

Assuming 7% follow-up losses, the final sample size required will be of 260 patients for the experimental group and 130 patients for the control group, i.e. a total of 390 patients.

Because the triple antiretroviral therapy based on a PI boosted with ritonavir (control treatment) has been widely studied for a practical sense, it has been considered to allocate the sample to twice the experimental treatment (1:2, respectively) [24 ], [26].

This distribution of the sample (1:2) compared with the distribution of equal groups (1:1) ensures greater security in the contrast of the study to a possible greater variability of response in the quality of life in the experimental group since this group is expected to more patients with diarrhea to begin new therapy. [27]

Also it will provide an improved accuracy in estimating mean and smaller confidence intervals, for example, more than 1% in the estimated proportions near 50%.

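### A block size of 4 cannot hold the 1:2 allocation, so the randomisation list in Protocol section 5.3 cannot be built as specified

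*Protocol*

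**What the plan says.** Protocol section 5.3 sets the block length and its purpose in one sentence: "The size of the blocks will be 4 to try to balance the treatment arms of the total sample and within each center". It adds "No stratification was planned by any other factor", which makes centre the only stratum. The same section then says "Patients will be randomized in a 1:2 ratio to one of the following two options", control being A and experimental B.

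The ratio is stated consistently elsewhere. The Synopsis has "Patients will be randomized in a 1:2 ratio to two groups, A and B respectively", and section 6.1 gives "130 patients in control group A and 260 patients in experimental group B", 390 in all. The sample size text in section 12 computes 124 and 248 evaluable patients at 1:2 and gives reasons for choosing that ratio.

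No section mentions a second block length, a varying block composition or another device that would reconcile a block of 4 with 1:2.

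**The concern.** A permuted block keeps an allocation ratio only if the ratio divides its length into whole patients. At 1:2 the length must be a multiple of 3, and 4 is not. Section 5.3 therefore gives the person who builds the list two instructions that cannot both be followed within a block.

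That person would have to depart from the stated ratio, depart from the stated block length, or use a construction that the protocol does not describe. The arm sizes, the power and the balance within centres then depend on a choice that nobody has written down. This is not a detail left to the statistical analysis plan, because the protocol itself fixes the block length.

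**Working it through.** **Inputs, all from the protocol.** Block length 4 and ratio 1:2 (section 5.3). Planned arms 130 and 260 (section 6.1). From the sample size text in section 12: "the mean baseline quality of life score measured with the MOS-HIV questionnaire was 61.84"; SD from the range, "e.g. 100) divided by 5, which gives 20"; effect, "will improve by 10% (e.g. to scores of 68.02) in patients assigned to the experimental group"; two-sided alpha 0.05; power 80%; 372 evaluable patients.

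**1. The plan's own sample size.** Difference = 0.10 × 61.84 = 6.184. With two experimental patients per control patient:

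n(control) = (1 + 1/2) × SD² × (1.960 + 0.842)² / difference² = 1.5 × 400 × 7.849 / 38.24 = 123.2, rounded up to 124.

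Experimental = 248 and total = 372. This matches the protocol exactly, so the plan does rest on 1:2.

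**2. Can a block hold 1:2?** Control places per block = length / 3.

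| Block length | Control | Experimental | Possible? |
|---|---|---|---|
| 3 | 1 | 2 | yes |
| 4 | 1.33 | 2.67 | no |
| 6 | 2 | 4 | yes |
| 9 | 3 | 6 | yes |

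**3. What uniform blocks of 4 would give.** The whole-number compositions nearest to 1:2 are 1:3 and 2:2 (control to experimental). Over 390 patients they give about 97.5:292.5 and 195:195.

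Power at 372 evaluable = Φ(6.184 / SE − 1.960), with SE = 20 × √(1/nA + 1/nB):

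| Composition | nA : nB | SE | Power |
|---|---|---|---|
| 1:2 (planned) | 124 : 248 | 2.200 | 80.3% |
| 1:3 | 93 : 279 | 2.395 | 73.3% |
| 2:2 | 186 : 186 | 2.074 | 84.7% |

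**4. Could blocks of 4 still total 130:260?** Yes, if compositions are mixed. Take 65 blocks of 1:3, 32 blocks of 2:2 and a last pair split 1:1:
- control = 65 + 64 + 1 = 130
- experimental = 195 + 64 + 1 = 260

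No single block then holds 1:2. A centre that fills three blocks has 4:8 only if it happens to draw two 1:3 blocks and one 2:2 block. Three of one kind give 3:9 or 6:6.

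**5. Blocks that fit.** 390 / 3 = 130 blocks of 1:2, and 390 / 6 = 65 blocks of 2:4. Each gives exactly 130:260 if the blocks are filled.

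**6. Predictability (secondary).** An allocation is determined once the other arm's places in the block are used up. This assumes that site staff know the length and the composition.
- Block of 3 (one A, two B): the three orders leave 2, 1 and 1 places determined. (2 + 1 + 1) / 3 = 1.33 per block, and 1.33 / 3 = 44.4%.
- Block of 4 at 1:3: (3 + 2 + 1 + 1) / 4 = 1.75, and 1.75 / 4 = 43.75%.
- Block of 4 at 2:2: (2 + 2 + 1 + 1 + 1 + 1) / 6 = 1.33, and 1.33 / 4 = 33.3%.
- Block of 6 at 2:4: the 15 orders leave 26 places determined in total. 26 / 15 = 1.73, and 1.73 / 6 = 28.9%.

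**The case against.** The best defence is that section 5.3 fixes a length, not a composition. A reader might infer that 130:260 is out of reach overall. The documents do not support that, because the mixed list in step 4 gets there. What stands against the defence is that the protocol describes no such list, and that mixed blocks do not deliver the balance within centres for which the blocks were introduced.

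Other stronger readings also fail:

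- *A definite loss of power.* The protocol states neither 1:3 nor 2:2, and 2:2 would raise power. The planned ANCOVA remains valid with unequal arms, so the contradiction by itself biases no estimate. Power should also be judged at the 372 evaluable patients in section 12, not at all 390.
- *390 is not a multiple of 4.* This is no defect. With blocks per centre, the last block in any centre may be incomplete at any length.
- *Drug supply is miscalculated.* Section 7.4 states no quantity and no assumption about arm sizes.
- *Allocation is compromised.* The trial is open label, blocking is by centre and the length is printed in the protocol, so inference from past allocations is possible. But section 5.3 keeps the list central and hidden, and a faxed page confirms eligibility before the allocation is given by telephone. These steps limit what a site can do with a guess, though they do not stop the guess. The shares in step 6 need a known uniform composition, which the protocol does not give, and a fixed block of 3 would be no less predictable than a block of 4.

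**Conclusion.** Wrong as written. A block of 4 and a 1:2 ratio cannot hold together, and no other section resolves the conflict. The block length is the statement that does not fit, since the ratio is repeated, justified and built into the sample size. This part is plain arithmetic and rests on no assumption.

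The size of the consequence is conditional. With uniform blocks of 4, power would be about 73% (1:3) or 85% (1:1) instead of 80%, given the protocol's difference, SD and 372 evaluable patients. With a mixed list the totals could be as planned, but 1:2 balance within small centres would not be assured. Predictability is a real but secondary weakness. It shows what could be inferred, not that any bias occurred.

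**What to change.** Replace the block length in section 5.3 with a multiple of 3, and say that the list is generated per centre. A length of 6, with 2 control and 4 experimental patients, would do. If a list already exists, check how it was built and document that, including the composition of its blocks.

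As a secondary improvement, vary the lengths at random among multiples of 3 and record them only in the restricted randomisation file, so that the protocol says no more than that permuted blocks are used within centre. Changing to a fixed block of 3 would correct the contradiction but leave 44% of allocations open to deduction.

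The cost is one amended sentence, handled under section 11.4, and a list check or a regenerated list. No patients or visits are added. The small downside of longer or varied blocks is slightly looser balance in centres that recruit few patients. The protocol gives no centre sizes from which to judge this.
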